#### Cognitive Assessment

The estimated verbal and visual IQ will be evaluated by the vocabulary and the matrix reasoning subtests of the Wechsler Intelligence Scale for Children—fifth edition (WISC-V Spanish version) (47) to control for potential differences in IQ between groups at baseline.

*Attention and speed* will be measured by the forward digit span and forward picture span (WISC-V), Children's Color Trail Test (CCTT) (48), the Five Digits Test (49), and Conners' Continuous Performance Test 3 (CPT3) (50).

The main subdomains comprising executive functions proposed by Diamond (2013) will be assessed. *Cognitive flexibility* will be evaluated by the Five Digits Test and the Children's Color Trail test (CCTT-2). *Working memory* will be assessed by the backward digit span (WISC-V), the backward picture span of the Weschler Non-verbal Scale (WNV) (51), and by an N-back task. *Inhibitory control* will be assessed by the Five Digits Test and a Go-no-go task. *Planning* will be measured by the Tower of London (52). Moreover, the Behavior Rating Inventory of Executive Function (BRIEF) will be administered (53).

We will consider global cognition as a primary measure. Attention and executive function subdomains will be further analyzed by a *post-hoc* analysis with Bonferroni correction for multiple comparisons.

#### Food Choice Registry

During the training period and for 1 week at 12 months' follow-up, participants will send pictures of the daily intake of food and drinks. These will be collected in tables quantifying the type of food per day and week. We will also administer the Kidmed questionnaire (54) at T0, T1, and T2.

A change in food choice will also be considered a primary measure.

#### QoL and Behavioral Measures

We will assess QoL by the Pediatric Quality of Life Inventory (PedsQL v4.0) (55) that includes parent- and self-reported scales of physical, emotional, social, and school functioning. Children's self-esteem and support perceived from classmates, parents, teachers, and friends is assessed by the Self-Perception and Social Support Profile for Children (56), and anxiety and depression by the Child Behavior Checklist (CBCL), a rating scale assessing behavioral and emotional symptoms in children (57) (www.aseba.org).

Changes in these measures will be considered secondary outcomes, resulting from a significant change in the previous ones (anthropometric and cognitive measures).

#### Connectivity Changes: MRI Assessment

All participants will undergo a 3T brain-MRI acquisition at baseline (T0), after treatment (T1), and after 12 months (T2). The scanning protocol will include structural and functional acquisitions. The MRI sequences will be the following: (1) high-resolution three-dimensional T1-weighted images acquired in the sagittal plane (MPRAGE sequence: TR = 2,400 ms, TE = 3.32 ms, TI = 1,000 ms, 256 slices, FOV = 224 mm; flip angle = 8°; 0.8 mm isotropic voxel); (2) 3D T2-weighted images in sagittal orientation (TR = 3,200 ms, TE = 298 ms, 256 slices, FOV = 224 mm; 0.9 mm isotropic voxel); (3) diffusion tensor imaging sequence (DTI) (single-shot diffusion-weighted EPI, *b* = 1,000 mm^2^/s, 30 directions, TR = 7,700 ms, TE = 89 ms, FOV = 244 mm; 2 mm isotropic voxel). Each direction will be acquired twice (AP and PA) and images will be averaged, improving signal-to-noise ratio; (4) resting state fMRI sequence (gradient-echo echo-planar imaging–EPI sequence) (240 volumes; 40 axial slices; TR = 2,500 ms; TE = 28 ms; FOV = 240 mm; flip angle = 80°; 3 mm isotropic voxel); (5) clinical sequences: a gradient T2 sequence (TR = 518 ms; TE = 20 ms; FOV = 240 mm; flip angle = 20°, voxel = 0.8 mm × 0.8 mm × 3 mm) and an axial FLAIR sequence (TR = 9,000 ms; TE = 96 ms; TI = 2,500 ms, FOV = 240 mm; flip angle = 150°, voxel = 0.9 mm × 0.9 mm × 3mm).

Brain plasticity will be assessed by computing brain connectivity through the analysis of DTI and resting-state fMRI sequences. It will be considered a primary measure. However, its analysis needs to be performed *post-hoc* with multiple comparisons' correction (FEW, FDR). Structural and clinical imaging (T1-, T2-weighted, and clinical sequences) are acquired to ensure that there are no significant baseline differences in brain structure between groups.

### Data Analysis Plan

#### Demographic, Neuropsychological, and QoL Variables

For demographic variables, we will use a descriptive analysis of the variables and a comparative analysis between the training and control groups at baseline. We will use the χ^2^ test (and if this is not applicable, Fisher's exact) for categorical variables and Student's *t*-test (if not applicable, the Mann–Whitney *U*-test) for quantitative variables to check that randomization has successfully distributed the possible confounding variables (age, sex, IQ, manual dominance, socioeconomic, and educational status).

For the evaluation of the effectiveness of treatment on BMI and cognition, we will perform a general linear model for repeated measures analysis including these two variables as primary outcomes. We will perform further *post-hoc* analysis evaluating the effects on cognitive domains and emotional and QoL measures if appropriate. Means comparisons will be performed by Student's *t*-test, if the conditions of application are met and confounding variables have been well-controlled (otherwise, adjusted analyses will be performed by multiple regression). Multiple comparisons will be tested by Bonferroni correction. Effect size will also be calculated according to Hunter and Schmidt (58). All statistical tests will be carried using a two-sided test with the significance level set at 5% with the software Statistical Package for the Social Sciences (SPSS, version 24.0) or R (version 3.6.3).

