## Materials and Methods

### Study Design

The design is a randomized controlled double-blind trial with 12 months of follow-up. Patients meeting study criteria are randomly allocated according to a sequential number into the “executive functions training” or “control task training” groups after given written informed consent to the coordinator of the project ([name]). A sample of the informed consent can be found in Supplementary Material 1. Randomization is stratified by sex, age (9–12 years), and manual dominance. The same person is the one in charge of monitoring training compliance, so the rest of the team is blind to group allocation. All neuropsychological assessments are performed by an independent psychologist ([name]), blinded to group allocation. Patients and families are also blind to the study-group allocation. Because the intervention has no possible side effects, there are no circumstances under which unblinding is permissible. This protocol report follows the SPIRIT and CONSORT reporting guidelines (26, 27).

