#### Sample Size

We attempt to achieve a total sample size of 30 subjects who have completed the treatment (training rate >70% of the days) and with a complete neuropsychological and MRI post-treatment assessment, 15 children per group. Previous literature on the field has shown significant results with similar sample sizes. Boutelle et al. (34) described a significant decrease in the percentage of eating (*d*_ppc2_ = 0.6, medium effect size) and ingested kcal (*d*_ppc2_ = 0.64, medium size), after training attention in a sample of 14 children (vs. 15 children doing a control task), showing far-transfer effect. Also, Verbeken et al. (35) reported a reduction in BMI (at 2-month follow-up; η_p_2 = 0.16, *d*_ppc2_ = 0.20, small effect) and improvement in short-term visual memory (Corsi block tapping task-forward; η_p_2 = 0.13, *d*_ppc2_ = 0.75, large effect), visual working memory (Corsi block-backwards; η_p_2 = 0.14, *d*_ppc2_ = 0.53, medium effect; BRIEF working memory; η_p_2 = 0.10, *d*_ppc2_ = 0.22), and meta-cognition (BRIEF; η_p_2 = 0.12, *d*_ppc2_ = 0.71) after training 22 children with obesity in visual working memory (vs. 22 children in passive control group). Also, Verbeken et al. (36) showed that an inhibition control and attentional training could significantly reduce inhibition problems (BRIEF; η_p_2 = 0.26, *d*_ppc2_ = 1.91, large effect) in a sample of 22 children with obesity (vs. 15 children in the passive control group).

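### For means comparisons, judged baseline balance decides between an unadjusted t-test and an adjusted regression; one pre-specified, baseline-adjusted model should replace this rule

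*Protocol article*

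**What the plan says.** All references are to the protocol article.

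- **Baseline tests.** The section on demographic, neuropsychological and QoL variables compares the arms at baseline by χ² or Fisher's exact test and by t-test or Mann–Whitney test. The purpose is "to check that randomization has successfully distributed the possible confounding variables". Six variables are listed: age, sex, IQ, handedness, socioeconomic status and education.
- **Rule for adjustment.** Later in the same section, means are compared by Student's t-test "if the conditions of application are met and confounding variables have been well-controlled (otherwise, adjusted analyses will be performed by multiple regression". No other criterion for adequate control is given.
- **Main model.** Between these two statements, the effect on BMI and cognition is assigned to a general linear model for repeated measures. No covariates are named.
- **Design.** Under Study Design: "Randomization is stratified by sex, age (9–12 years), and manual dominance". These are three of the six variables tested at baseline.
- **Outcome scale.** Table 1 defines the primary outcomes as changes from baseline.

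**The concern.** In a randomised trial, baseline differences are due to chance by design. A significance test of them therefore says little about whether adjustment is worthwhile; what matters is how strongly the covariate predicts the outcome. Letting such a test choose the model has three drawbacks here.

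1. It is insensitive in a trial this small.
2. It can switch the method by chance when randomisation is sound.
3. It looks at the wrong variables. The stratification factors belong in the model because of the design, whatever a test shows. The outcome's own baseline value, usually its best predictor, is not on the list.

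At stake is precision in the comparisons that the rule governs, and protection against an unlucky imbalance that happens not to reach significance.

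**Working it through.** **Inputs.** "All statistical tests will be carried using a two-sided test with the significance level set at 5" percent. Size: "We attempt to achieve a total sample size of 30 subjects who have completed the treatment", that is, "15 children per group". The sample size section argues from precedent and states no power, SD or target difference, so there is no planned figure to reproduce. For illustration I use d = 0.6, the value given for a cited study that "described a significant decrease in the percentage of eating". The enrolment section implies 22 − 6 = 16 and 17 − 2 = 15 children who met the training requirement so far. The correlation r between T0 and follow-up is not in the document; values of 0.5 to 0.9 are assumed.

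**Step 1: sensitivity of a baseline test.** At 15 per arm the smallest significant difference is t(0.975, 28 df) × √(2/15) = 2.048 × 0.365 = 0.75 SD. For a true difference of 0.5 SD the noncentrality is 0.5 × √(15/2) = 1.37 and power is 0.262. With 16 and 15 children the standard error of a chance difference is √(1/16 + 1/15) = 0.359 SD. A simulation gave a difference of at least 0.5 SD in 16.5% of trials. A 5% test flags 0.05/0.165 = 30% of these at most, which leaves 70% unflagged; the simulation also gave 70%.

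**Step 2: switching by chance.** With six independent tests, P(at least one significant) = 1 − 0.95⁶ = 0.265. If stratification keeps its own three factors balanced and only the other three can trigger a switch, 1 − 0.95³ = 0.143.

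**Step 3: precision.** In units of SD², with equal variances at both visits, the variances are 1 for a final-value comparison, 2(1−r) for a change score (equivalent to group-by-time with two visits) and 1−r² for ANCOVA. The ANCOVA-to-change ratio is (1−r²)/[2(1−r)] = (1+r)/2. Power is for d = 0.6 at 15 per arm.

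| r | ANCOVA / final value | ANCOVA / change | Power, final value | Power, change | Power, ANCOVA |
|---|---|---|---|---|---|
| 0.5 | 0.75 | 0.75 | 0.355 | 0.355 | 0.448 |
| 0.6 | 0.64 | 0.80 | 0.355 | 0.426 | 0.508 |
| 0.7 | 0.51 | 0.85 | 0.355 | 0.535 | 0.602 |
| 0.8 | 0.36 | 0.90 | 0.355 | 0.708 | 0.752 |
| 0.9 | 0.19 | 0.95 | 0.355 | 0.944 | 0.953 |

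**Step 4: imbalance that passes the test.** 8,000 null trials were simulated per value of r, at 15 per arm. An imbalance of 0.5 to 0.75 SD in the outcome's T0 value, below the threshold of Step 1, arose in about 13% of trials. Rejection rates within those trials at r = 0.5 / 0.7 / 0.9 were:

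- final-value t-test: 10.4% / 13.8% / 15.3%
- change score: 10.5% / 5.6% / 5.5%
- ANCOVA: 4.6% / 4.4% / 4.3%

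Over all trials the final-value t-test rejected in 5.1% / 4.7% / 4.8%.

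**The case against.** **Scope.** The rule follows the sentence on post-hoc analyses and speaks of means comparisons. BMI and cognition have the repeated-measures model, food choice has linear mixed models, and imaging has a general linear model. No primary model is clearly governed by the rule. This stands, and the point is confined to the means comparisons. The text does not say which comparisons these are, or whether they use final or change values.

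**The link is inferred.** The protocol never says that a baseline p-value triggers the switch. That is correct. But the baseline tests are the only check described, and without them the choice would rest on judgement after the data are seen, which is no better.

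**Covariates may be listed in an analysis plan that is not shown.** This stands for a covariate list as such, whose absence is no finding. It does not rescue the conditional rule: that rule is stated, and a fixed model elsewhere would contradict it.

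**Validity.** Average type I error stays near 5%, and stratification already gives some protection for three of the six variables. Both stand.

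**Stronger readings that the document does not support.**

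- A reader might infer that baseline information goes unused and that imbalance in BMI or cognition is left uncorrected. With T0 among the repeated measures, the group-by-time test uses it.
- A reader might infer that the effect is read from a group main effect averaged with T0, and so diluted. The plan names no such effect, and Table 1 points to change from baseline.
- A reader might see the same rule in the MRI section, which speaks of ensuring that there are no significant structural differences at baseline. That sentence explains why sequences are acquired; no analysis choice depends on it.

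**Conclusion.** The point holds in limited form. For means comparisons, the protocol makes adjustment depend on baseline balance, and the only check described is insensitive at 15 per arm (26% power for 0.5 SD), liable to chance switching (26% with six independent tests, 14% if only three can trigger it) and blind to the outcome's own baseline value.

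The size depends on what is compared. Against t-tests on final values, ANCOVA variance is 0.64 to 0.19 of the unadjusted variance for r from 0.6 to 0.9. Against the group-by-time test for BMI and cognition the reduction is only 20% to 5% over the same range. These figures rest on assumed correlations and equal variances; the chance-switching figure also assumes independent tests. The trial is not invalidated, but the weakness is easily corrected and falls where precision is scarce.

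**What to change.** Delete the conditional rule and specify one model per outcome, used whatever the baseline tables show:

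- ANCOVA or a constrained mixed model, with T1 and T2 values as outcomes
- fixed covariates: the T0 value of the same measure, sex, age and handedness, with handedness dropped in advance if it is nearly constant
- group contrasts at T1 and at T2
- baseline tables kept descriptive, with no p-values used to choose a model.

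These variables are already collected. The cost is about four degrees of freedom: with 30 children in a single-visit ANCOVA, the residual falls from 28 to 24. For that reason the covariate set should stay this small.

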#### Food Choice

To test our hypothesis that along the training weeks participants will make healthier and more balanced food choices, we will compute the content of the tables and analyze them by linear mixed models for longitudinal data. Multiple comparisons will be tested by Bonferroni correction. We will also assess the difference between groups at 12-month follow-up.

#### Imaging Data

To compute brain connectivity and perform graph-theoretical analysis, we need to preprocess MPRAGE, fMRI, and DTI data sets altogether. Thus, we can perform structural (by probabilistic or deterministic tractography) and functional connectivity analyses, i.e., parcellating the brain into functionally related areas using an atlas [i.e., the AAL atlas by (59)]. The mean time series of the obtained regions' voxels can be used to calculate cross-correlations between them, thus obtaining an *n* × *n* correlation matrix that represents each subject's connectivity profile.

To do that, we will segment the MPRAGE images by the automated FreeSurfer stream (version 5.3; available at https://surfer.nmr.mgh.harvard.edu/) into different cortical regions. With FSL [FMRIB's Software Library, http://www.fmrib.ox.ac.uk/fsl/; tract-based spatial statistics (TBSS) and tractography Diffusion Toolbox (FDT)], we will analyze the DTI dataset. After individual FA map extraction, a probabilistic tracking algorithm is used to estimate white matter pathways connecting different regions of interest. Again, a general linear model, correcting for multiple comparisons across space, will be used to compare differences among groups. Finally, we will preprocess functional images (fMRI) using FSL and AFNI (Analysis of Functional NeuroImages, https://afni.nimh.nih.gov/). An independent component analysis (ICA) can be carried out using tensorial independent component analysis as implemented in MELODIC part of FSL. This enables to obtain a set of independent components and identify the common resting-state functional networks (60).

Brain plasticity will be assessed by *post hoc* analysis with a correction for multiple comparisons (FWE, FDR).

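### The only ICA variant named for the resting-state fMRI, tensor ICA, assumes a time course common to all children; its child-level scores would be almost uninformative if used to compare arms

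*Protocol article*

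**What the plan says.** Under Connectivity Changes: MRI Assessment, the protocol article lists one functional acquisition, a "resting state fMRI sequence (gradient-echo echo-planar imaging" sequence with "240 volumes; 40 axial slices; TR = 2,500 ms". No in-scanner task is described. The same section gives connectivity its role: "Brain plasticity will be assessed by computing brain connectivity through the analysis of DTI and resting-state fMRI sequences. It will be considered a primary measure".

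Under Imaging Data, two functional routes appear. The first is an atlas parcellation that gives each child a region-by-region correlation matrix. The second is the ICA, which "can be carried out using tensorial independent component analysis as implemented in MELODIC part of FSL". Its stated purpose follows: "This enables to obtain a set of independent components and identify the common resting-state functional networks". Tensor ICA is the only ICA variant named. The text does not say which ICA output, if any, enters a comparison of the arms.

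**The concern.** Tensor ICA suits data in which every subject's signal follows the same timing, as in a task with identical stimulus onsets. At rest nothing aligns one child's fluctuations with another's. The method named and the scan acquired therefore do not fit each other, and this can be read from the article itself without any fuller plan.

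The quantity at risk is the score that tensor ICA assigns to each child. It is the natural child-level output of this decomposition, and assessing plasticity through the ICA needs some child-level quantity. If the time course is wrong, the score mainly reflects how far a child's signal happens to line up with an arbitrary common series, and hardly at all how strong the network is in that child. A null result on such scores could be misread as no plasticity. The target is only 15 children per group, so little information can be spared.

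**Working it through.** The plan gives no power, effect size or SD for the fMRI outcome, so there is no stated figure to reproduce. The check is of the model structure, then by simulation.

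**Inputs from the article.** 240 volumes at TR 2.5 s (240 × 2.5 = 600 s, or 10 minutes); 15 children per group (Sample Size); two-sided 5% level (Data Analysis Plan, where it is stated with the neuropsychological analyses).

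**Assumptions not in the article.** Signal limited to 0.01-0.1 Hz; between-child coefficient of variation (CV) of network amplitude 0.2 or 0.4; noise SD 0.3; true difference between arms d = 0, 0.65, 1.0 or 1.5. One network with a known spatial map, which favours tensor ICA.

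**Model.** For child s at time t, the signal is y(t,s) = a(s) × x(t,s) + noise, where a(s) is the child's network amplitude. Tensor ICA replaces x(t,s) by a common x(t), so the time-by-child matrix is reduced to its rank-1 approximation. The child scores are the leading right singular vector. The comparator is the SD of each child's own series. Both were compared between arms by t-test, with 1,500 runs per setting (Monte Carlo standard error at a 5% rate: √(0.05 × 0.95/1500) = 0.006).

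**Rejection rates when time courses are independent between children (resting data)**

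| d | Tensor score, CV 0.2 | Tensor score, CV 0.4 | Child-specific, CV 0.2 | Child-specific, CV 0.4 |
|---|---|---|---|---|
| 0 | 0.032 | 0.023 | 0.057 | 0.045 |
| 0.65 | 0.034 | 0.018 | 0.398 | 0.381 |
| 1.0 | 0.040 | 0.036 | 0.738 | 0.737 |
| 1.5 | 0.047 | 0.031 | 0.975 | 0.978 |

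The shared component explains 8-11% of the variance. For scale, a series that matched one child and no other would explain 1/30 = 3.3%. The tensor score correlates 0.21-0.30 with true amplitude.

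**Control: time courses truly shared.** The tensor score then works. The shared component explains 92-96% of the variance, the correlation with amplitude is 1.00, and rejection is 0.39-0.42, 0.75 and 0.98 at d = 0.65, 1.0 and 1.5. The fault is thus the mismatch between method and data.

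**Cross-check of the comparator.** The normal approximation is power = Φ(d × √(15/2) − 1.96), with √7.5 = 2.739.
- d = 0.65: Φ(1.780 − 1.96) = 0.43
- d = 1.0: Φ(2.739 − 1.96) = 0.78
- d = 1.5: Φ(4.108 − 1.96) = 0.98

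The simulated child-specific rates agree, allowing for the t distribution.

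**A harder setting.** A small run (60 repeats, five overlapping networks, maps estimated, d = 1.0, 15 per arm) gave 9% of variance for the shared component and a correlation of 0.19 with amplitude. Rejection was 7% on signed and 13% on absolute scores, against 47% on child-specific amplitudes. With 60 repeats the standard error of the 13% is √(0.13 × 0.87/60) = 0.04. In the same run the group maps were recovered about equally well by the tensor and the concatenated estimate (mean correlation with truth 0.77 for both).

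**The case against.** The strongest reply is that the article never commits to the test simulated here. The ICA is worded as an option, and its only stated use is to identify networks common to the group. The general linear model for comparing groups is described after the DTI steps. How ICA output reaches a group test is a detail that a condensed article may leave to a fuller plan, so its absence is no defect. All of this stands, and it makes the concern conditional: the rejection rates apply only if the tensor scores are used at child level.

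Three stronger readings are tempting, and the documents support none of them.
- **A true training effect on connectivity would be lost.** The atlas correlation matrices use each child's own time series, and the DTI analysis does not involve the ICA. The primary measure is defined by DTI and resting-state connectivity, not by ICA scores.
- **The network maps would be unstable or artefactual.** The one check that estimated maps found no disadvantage for the tensor estimate.
- **The scores cannot show a difference.** A weak correlation with amplitude remains, and absolute scores rejected slightly more often than 5% in the small run.

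The reply does not remove the mismatch itself. A specific variant is named, it is the only one, and its central assumption does not hold for the only functional scan. That is a statement in the text and not a matter of silence.

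**Conclusion.** The point holds in a limited form. Tensor ICA is ill-suited to the resting-state data that the article describes. Should its child-level scores be used to assess plasticity or compare arms, they would detect a difference little or no better than chance: about 2-5% rejection up to d = 1.5 with 15 per arm, against about 74% (d = 1.0) and 98% (d = 1.5) for child-specific estimates.

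These figures rest on the assumed amplitude spread, noise and effect sizes. They cover a group difference in the amplitude of one network at one time point, without the planned FWE or FDR correction. The child-specific rates are therefore a best case, and the contrast matters more than the levels. One optional route to a primary measure is affected, and the connectivity outcome as a whole is not invalidated. The point is worth acting on because the repair is cheap and a null result from the tensor scores would be hard to interpret.

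**What to change.** Under Imaging Data, replace the tensor option with temporally concatenated group ICA in MELODIC, run blind to arm. Follow it with dual regression to obtain each child's network maps at T0, T1 and T2. State that the arms will be compared on those maps with the FWE/FDR correction already planned. The atlas-matrix and DTI text can stay as it is.

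The cost is a short change of wording and slightly more computing. Software and scans stay the same, and no new data are needed.
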